### Setting and recruitment

This study will be performed at SUMHS in China. Data collection and exercise training will occur at the campus of this university. Recruitment of eligible participants will be conducted by two research assistants independently and will be achieved with the use of campus radio, flyers, and WeChat. Figure 2 shows the SPIRIT schedule of assessments and interventions. Formal recruitment for the study began in May 2018.

**Fig. 2 Fig2:**
[figure not shown]
SPIRIT figure showing schedule of interventions and assessments

### Participant eligibility

The eligible participants should fulfill the study inclusion criteria and not comply with the exclusion criteria. For inclusion, the participant should be aged 16 to 25 years, be able to provide a signed informed consent form, and be a full-time student at first or second grade. Criteria for exclusion from the study are as follows: being or having been engaged in a long-term regular practice of Baduanjin; being a member of the Martial Arts Association, Dance Association, Aerobics Association, Sanda Association, or Taekwondo Association; or having had severe cardiovascular diseases, musculoskeletal system diseases, or other sports contraindications.

### Randomization, allocation, and blinding

The random allocation sequence will be produced by an independent statistician via the PLAN sentences of the statistical software SAS 9.1. The random allocation sequence will be managed by an assigned project manager who will not take part in the participants’ recruitment, and it will be concealed from those research assistants who will be responsible for recruitment or outcome assessment. After signing the informed consent and undergoing baseline assessment of primary and secondary outcome measures, the eligible participants will receive their information of allocation result via WeChat. They will be allocated randomly into either the Baduanjin exercise group or the control group.

Although both the participants and exercise coaches cannot be blinded in this trial, we will blind the outcome assessors and statistics analyzers by the following procedures. Participants’ outcomes will be measured by two special investigators who are not involved in the allocation and exercise intervention. Before the outcome measurement starts, participants, exercise coaches, and the related research assistants will be told not to reveal any information about the allocation. The statistical analysis will be performed by a statistician who does not participate in the implementation of the trial, and the allocation information of the groups will be concealed by a blind code. The blind code will be disclosed when the statistical analysis is completed.

### Intervention

#### Baduanjin exercise group

Participants in the Baduanjin exercise group will be assembled at the gymnasiums of the university and will receive Baduanjin exercise training at a frequency of 4 days per week, 1 h per day, for 12 weeks. The training scheme originated from *Health Qigong - Baduanjin,* published by the General Administration of Sport of China [35]. The whole set of Baduanjin exercises consists of eight postures (Fig. 3). Two qualified coaches will be employed to teach the participants the correct Baduanjin postures and supervise them during the entire intervention period.

**Fig. 3 Fig3:**
[figure not shown]
The Baduanjin exercise postures

#### Control group

The participants in the control group will not receive any specific exercise training during the 12-week intervention period. They will be instructed to maintain their original lifestyle.

All participants in both the Baduanjin exercise group and the control group will be required to record their daily physical activity by using a step counter in their mobile phone and to record exercise information during the 12-week intervention period.

#### Outcome assessment

Outcome measurement of participants will be performed at the campus gymnasium by physical education teachers who do not participate in the implementation of this trial. Primary and secondary outcomes will be assessed at baseline and after the 12-week intervention period.

#### Primary outcome

According to China’s National Student Physical Health Standard (2014 Revision) [36], the health-related physical fitness measurements consist of body mass index (BMI), vital capacity (VC), 50-m running, body anteflexion in sitting position (BAISP), standing long jump (SLJ), pull-ups per minute (male)/sit-ups per minute (female), and 1000-m running (male)/800-m running (female). Overall assessment of health-related physical fitness is evaluated using a composite point which is calculated as the summation of the points of each measurement multiplied by the participant’s corresponding weight. A composite point of health-related physical fitness = 15%BMI points + 15%VC points + 20% 50 m running points + 10% BAISP points + 10% SLJ points + 10% pull-up (male)/sit-up (female) points + 20% 1000 m (male)/800 m (female) running points. The scoring standard and weight of each measurement are listed in Tables 1 and 2.
Body mass index will be assessed using the formula BMI = body mass (kg)/height (m)^2^. Body mass and height will be measured using the Height and Weight measuring instrument produced by Zhongtitongfang Co., Ltd., Beijing (product type ZTTF-CSTF-ST).Vital capacity, the maximum amount of air a person can expel from the lungs after a maximum inhalation, will be measured using the vital capacity tester produced by Zhongtitongfang Co., Ltd., Beijing (product type CSTF-FH-5000).Body anteflexion in sitting position is applied to evaluate the body flexibility of the lower back and hamstring muscles and will be measured by the “sit and reach” test using a “sit and reach” tester produced by Zhongtitongfang Co. (product type CSTF-TQ-5000). For the test procedure, the subject sits on the floor with legs stretched out straight ahead and the soles placed flat against the box; then the hands with the palms facing downward reach forward along the measuring line as far as possible. The point is recorded to the nearest centimeter as the distance reached by the hand.Standing long jump is a common test to assess the explosive power of the student’s legs and will be measured using the longitudinal jump tester produced by Zhongtitongfang Co. (product type CSTF-ZL-5000). The student stands behind a line marked on the ground with feet slightly apart, then attempts to jump as far as possible. The scoring is the distance jumped from take-off line to the nearest point of contact on the landing.Pull-ups are a common way to measure the upper body strength and will be measured using the chin-up tester produced by Zhongtitongfang Co. (product type CSTF-YT-5000). The subject grasps the overhead pull-up bar, then pulls the body up until the chin extends the bar. The point is the number of pull-ups per minute.Sit-ups measure the strength of the abdominal muscles and will be measured using the sit-ups tester produced by Zhongtitongfang Co. (product type CSTF-YW-5000). The subject lays down with the knees bent and the feet placed flat on the ground and the arms crossed over the chest; she then slowly sits up until the body is vertical, then slowly lays back down. The point is the number of sit-ups per minute.Cardiopulmonary fitness will be assessed using the step test, which is measured with the step tester produced by Zhongtitongfang Co. (product type CSTF-TZ-5000). The subject completes 30 up and down steps per minute for 3 min in accord with the rhythm, then measures the pulse at 1–1.5 min, 2–2.5 min, and 3–3.5 min after stopping the test. The index of step test = (duration of step moving (in seconds) × 100)/(2 × (sum total of three measured pulses)).The 50-, 800-, and 1000-m running test evaluates the capability of rapid running and reaction as well as aerobic fitness. It will be measured by the physical education teachers using a stopwatch at the campus recreation ground.

**Table 1 Tab1:** Scoring standard and weight of body mass index for health-related physical fitness of college students

BMI	100 (points)	80 (points)	60 (points)	Weight
Male	17.9–23.9 (kg/m^2^)	≤ 17.8 or 24.0–27.9 (kg/m^2^)	≥ 28.0 (kg/m^2^)	15%
Female	17.2–23.9 (kg/m^2^)	≤ 17.1 or 24.0–27.9 (kg/m^2^)	≥ 28.0 (kg/m^2^)	15%

**Table 2 Tab2:** Scoring standard and weight of each measurement for health-related physical fitness of college students

Points	Male						Female					
	VC (ml) W:15%	50 m (s) W:20%	BAISP (cm) W:10%	SLJ (cm) W:10%	Pull-ups (times/min) W:10%	1000 m (min:s) W:20%	VC (ml) W:15%	50 m (s) W:20%	BAISP (cm) W:10%	SLJ (cm) W:10%	Sit-ups (times/min) W:10%	800 m (min:s) W:20%
100	5040	6.7	24.9	273	19	3′17”	3400	7.5	25.8	207	56	3′18”
95	4920	6.8	23.1	268	18	3′22”	3350	7.6	24.0	201	54	3′24”
90	4800	6.9	21.3	263	17	3′27”	3300	7.7	22.2	195	52	3′30”
85	4550	7.0	19.5	256	16	3′34”	3150	8.0	20.6	188	49	3′37”
80	4300	7.1	17.7	248	15	3′42”	3000	8.3	19.0	181	46	3′44”
78	4180	7.3	16.3	244		3′47”	2900	8.5	17.7	178	44	3′49”
76	4060	7.5	14.9	240	14	3′52”	2800	8.7	16.4	175	42	3′54”
74	3940	7.7	13.5	236		3′57”	2700	8.9	15.1	172	40	3′59”
72	3820	7.9	12.1	232	13	4′02”	2600	9.1	13.8	169	38	4′04”
70	3700	8.1	10.7	228		4′07”	2500	9.3	12.5	166	36	4′09”
68	3580	8.3	9.3	224	12	4′12”	2400	9.5	11.2	163	34	4′14”
66	3460	8.5	7.9	220		4′17”	2300	9.7	9.9	160	32	4′19”
64	3340	8.7	6.5	216	11	4′22”	2200	9.9	8.6	157	30	4′24”
62	3220	8.9	5.1	212		4′27”	2100	10.1	7.3	154	28	4′29”
60	3100	9.1	3.7	208	10	4′32”	2000	10.3	6.0	151	26	4′34”
50	2940	9.3	2.7	203	9	4′52”	1960	10.5	5.2	146	24	4′44”
40	2780	9.5	1.7	198	8	5′12”	1920	10.7	4.4	141	22	4′54”
30	2620	9.7	0.7	193	7	5′32”	1880	10.9	3.6	136	20	5′04”
20	2460	9.9	−0.3	188	6	5′52”	1840	11.1	2.8	131	18	5′14”
10	2300	10.1	−1.3	183	5	6′12”	1800	11.3	2.0	126	16	5′24”

Abbreviations: *W* weight, *VC* vital capacity, *BAISP* body anteflexion in sitting position, *SLJ* standing long jump

#### Secondary outcomes

Handgrip strength, which is used to determine the maximum isometric strength of the hand and forearm muscles, will be measured using the handgrip strength dynamometer produced by Zhongtitongfang Co. (product type CSTF-WL-5000). The subject holds the dynamometer in the hand with the arm at a right angle and the elbow by the side of the body, then squeezes the dynamometer with maximum isometric effort. The best result from several tests for each hand will be recorded.

Body composition includes fat mass, body fat (percentage), fat-free mass, and lean body mass. These measurements will be taken by bioelectrical impedance analysis using an Inbody 720 (Biospace Co.), which emits a low-intensity electrical current that runs through the person’s body to measure resistance, reactance, and phase angle.

#### Safety measurements

Any unexpected adverse events (AEs) that occur during the 12-week intervention period will be reported to the research assistants, and the causality of Baduanjin exercise will be assessed. If serious AEs occur, the research assistants will report them to the project manager and ethics committee immediately; they will make a decision on whether the participant needs to withdraw from the study.

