#### Data collection

The demographic characteristics will be collected by the research assistants at the recruitment. The primary and secondary outcome data will be collected by the outcome assessors at baseline and at the end of the intervention. All data collection in this study will be performed using standardized procedures, and the outcome assessors will receive standard training on how to measure all outcomes to ensure equal testing conditions for all participants.

To promote participant retention and the provision of complete outcome data from all participants, a total incentive of up to 200 RMB per individual as compensation for their time participating in the study will be provided to all participants. The incentive will be delivered using the way of WeChat draw via WeChat after completion of the final assessment following the 12-week intervention.

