### Monitoring

Due to the low-risk nature of the aerobic exercise intervention, we do not anticipate any potential harms. Therefore, there will be no Data Monitoring Committee, interim analyses, or stopping rules.

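### The adverse-event window covers only the 12-week intervention, so the trial's own exertional fitness tests, held before and after it, fall outside the stated reporting rule

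*Protocol article*

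**What the plan says.** The protocol article, under Safety measurements, sets the reporting rule: "Any unexpected adverse events (AEs) that occur during the 12-week intervention period will be reported to the research assistants". It adds that "the causality of Baduanjin exercise will be assessed", naming no other possible cause. The next sentence deals with serious events: "If serious AEs occur, the research assistants will report them to the project manager and ethics committee immediately". That sentence gives no time window.

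The timing of the fitness tests is set elsewhere. Outcome assessment says "Primary and secondary outcomes will be assessed at baseline and after the 12-week intervention period", and the abstract and Study design agree. Randomization, allocation, and blinding puts the first session before participants learn their group: "After signing the informed consent and undergoing baseline assessment of primary and secondary outcome measures, the eligible participants will receive their information of allocation result". Data collection describes the incentive as paid "after completion of the final assessment following the 12-week intervention".

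The Primary outcome section describes the tests: timed 50-m and 800/1000-m runs, pull-ups or sit-ups per minute, a standing long jump and a 3-minute step test. The Monitoring section considers only the risk of the training: "Due to the low-risk nature of the aerobic exercise intervention, we do not anticipate any potential harms". Statistical analysis plans a list and a between-group test of adverse events, without giving a window of its own.

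**The concern.** A harms record should cover what the trial asks participants to do. Here the trial asks for two things: the training (in one arm) and two sessions of physical testing (in both arms). The stated window covers the first and leaves out the second. A fall in the sprint or a muscle strain in the long jump is a study-related event in a consented participant, yet under the written rule nobody has to report it.

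Two things are at stake. The first is participant protection and complete reporting: the trial could state that no adverse events occurred when the rule never asked about the test sessions. The second concerns interpretation of the data. An injury at the final session could cost a component of the primary composite (the 800/1000-m run carries 20% of the weight), and the adverse-event list, kept to its stated window, would not show why.

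**Working it through.** No formula or stated figure is involved. The check sets the reporting window against the test schedule.

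1. **Window.** Safety measurements: unexpected events in the 12-week intervention period, reported to the research assistants.

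2. **Baseline session.** Randomization, allocation, and blinding: "After signing the informed consent and undergoing baseline assessment of primary and secondary outcome measures" comes first, and allocation is disclosed afterwards. The intervention cannot start before allocation is known, so this session precedes the window. Consent has already been given.

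3. **Final session.** The abstract, Study design and Outcome assessment all place it after the 12 weeks, and the incentive sentence in Data collection has it following the intervention. Another sentence in Data collection is looser and puts collection at the intervention's end, which could be read as inside the window. Four statements point the other way, one of them in that same section. On the looser reading the baseline session would still be outside.

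4. **Any extension elsewhere?** None. Statistical analysis gives no window for the adverse-event comparison, and Monitoring addresses the risk of the training only.

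5. **Causality.** It is assessed for Baduanjin alone. Even if a test-session event were volunteered, the text gives no way to classify it as related to a test.

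6. **Serious events.** The sentence has no window. It could be read as standing alone and covering the whole trial. It could also be read as following from the sentence before it, since the same research assistants receive the windowed reports. The text does not settle which.

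7. **Extent.** Planned test visits: 120 × 2 = 240. With the assumed 20% loss, the second session has 120 × 0.80 = 96 participants, giving 120 + 96 = 216 visits. This counts exposure outside the window. The documents give no event rate, so no expected number of missed events can be derived.

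**The case against.** The strongest case for the plan is that the window suits its stated purpose, which is to judge whether Baduanjin causes harm. Events at the baseline session cannot be caused by Baduanjin, and since they precede knowledge of allocation they cannot bias the between-group comparison. Both arms take the same tests. The tests are items of a national student fitness standard, supervised by physical education teachers, and students with severe cardiovascular disease, musculoskeletal disease or other contraindications to sport are excluded. The article is condensed, and handling of incidents at test sessions may be described in the full protocol or on the case report form. Recruitment closed on 30 April 2019, so most or all baseline sessions have probably passed.

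Much of this stands. It limits the consequence, but it does not remove the gap. The article does not leave the window unstated; it states one, and that window excludes the test sessions. A purpose confined to Baduanjin does not explain why harm from other study procedures goes unrecorded.

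A reader might infer more than the text supports:

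- *That a collapse in the final run would not reach the ethics committee.* The serious-event sentence carries no window, so escalation is unclear and not excluded.
- *That all the tests are maximal, or the most strenuous part of the trial.* The step test has a fixed cadence and is not maximal. That the timed runs are harder than the training is a reasonable inference, but no section makes the comparison.
- *That a value lost through injury would leave no explanation anywhere.* Assessors complete a paper form at each session. It is not shown, and it may record reasons for missing data.

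**Conclusion.** The point holds as a gap in a stated rule. Under the article's wording, non-serious events at both test sessions fall outside adverse-event reporting, the position of serious events there is ambiguous, and relation to the tests is never assessed. This rests on reading the final session as after the 12 weeks, which most of the text supports; the baseline session is outside on any reading.

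The size is modest. The 216 to 240 visits outside the window should not be read as a measure of harm. The effect is on participant protection and the completeness of the harms report. The efficacy analysis is not shown to be wrong, and baseline-session events could not distort the comparison of arms. The change is worth making because it is specific and cheap, though with recruitment closed it can act prospectively mainly on the final assessments.

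**What to change.** In Safety measurements:

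- State the reporting window as running from informed consent to the end of the final assessment session.
- Say that serious-event reporting covers the same window.
- Assess relation to the test procedures as well as to Baduanjin.

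In Statistical analysis, list test-session events separately and keep the between-group comparison to events in the 12 weeks, so that baseline events shared by both arms are not mixed into it.

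For baseline sessions already completed, report events retrospectively where records exist and say that collection was retrospective.

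The cost is one adverse-event line on the paper form already completed at each assessment, a few more minor events to record, and a notification of the changed wording to the ethics committee. No endpoint, schedule or sample size changes.

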### Statistical analysis

Analysis of data in this trial will be performed by a statistician who is not involved in the trial. In descriptive analysis of the sample, continuous variables will be expressed by using the mean and standard deviation for normal distributions, and the median and interquartile range for non-normal distributions. Normality will be tested using the Kolmogorov–Smirnov test. Appropriate transformations will be applied in cases of non-normal distribution. Categorical variables will be expressed as proportions with their standard error.

Baseline characteristics between groups will be compared using the *t* test or Mann–Whitney test for continuous variables and Pearson’s χ-squared or Fisher’s exact test for categorical variables. If incomparability appears, the inequality factors will be treated as confounding variables in the final efficacy analysis.

For comparison of primary and secondary outcomes between groups, a *t* test or non-parametric tests will be used for continuous data, and Pearson’s χ-squared or Fisher’s exact test for categorical data at baseline and after intervention; the between-group differences (treatment effects) will be analyzed by using mixed linear models with restricted maximum likelihood using the group-by-time interaction terms. Analysis of the outcomes will be performed on the basis of the intention-to-treat (ITT) population. All participants who have been randomized will be included in the final analysis irrespective of compliance or withdrawal from the program. Full information maximum likelihood estimation will be employed for missing data.

AEs will be listed and analyzed using a χ-squared test or Fisher’s exact test. Severe AEs will be listed and described in detail.

All data will be analyzed with SPSS 21.0 (IBM, Chicago, IL, USA) software packages. Statistical significance is defined as a two-sided *P* value of < 0.05.

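### Adverse event reporting is limited to unexpected events, and contact differs by arm, so the planned test on AEs confounds harm with opportunity to report

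*Protocol article*

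**What the plan says.** Under Safety measurements, the protocol article sets the capture rule: "Any unexpected adverse events (AEs) that occur during the 12-week intervention period will be reported to the research assistants". It adds that "the causality of Baduanjin exercise will be assessed". It does not define *unexpected*.

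Under Statistical analysis it states: "AEs will be listed and analyzed using a χ-squared test or Fisher’s exact test". The words *between groups* do not appear in that sentence, but in a two-arm trial this is the natural reading.

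Contact during the 12 weeks differs by arm:

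- The Baduanjin group "will receive Baduanjin exercise training at a frequency of 4 days per week, 1 h per day, for 12 weeks", and two coaches "supervise them during the entire intervention period".
- For controls: "The participants in the control group will not receive any specific exercise training during the 12-week intervention period".

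Some contacts are shared. Both arms are assessed at baseline and after 12 weeks, and "All participants in both the Baduanjin exercise group and the control group will be required to record their daily physical activity", together with exercise information. The text does not link either of these sources to AEs.

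**The concern.** A chi-squared or Fisher test on AE counts compares the true risks only if an event has the same chance of entering the count in each arm. Two written choices work against that.

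First, limiting reports to unexpected events can remove the complaints an exercise programme would be expected to cause, such as strains or soreness. With no definition or list of expected events, whoever reports has to decide what qualifies.

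Second, one arm meets staff at 48 sessions, and no contact with the other is described between the two assessments. Participants and coaches are unblinded, so blinding does not equalise reporting. Causality is assessed for Baduanjin only, which also directs attention to one arm.

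The comparison could therefore show an excess with exercise that reflects closer observation. It could also look reassuring because foreseeable events were not counted.

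**Working it through.** **Inputs from the protocol article**

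- 120 participants allocated 1:1, so 120 / 2 = 60 per arm (Study design).
- Two-sided significance level 0.05 (Statistical analysis).
- Supervised sessions: 4 per week × 12 weeks = 48 in the Baduanjin arm (Intervention); none described for controls.

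The article gives no AE rate, capture rate or AE power, so there is no stated figure to reproduce.

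**Assumed inputs**

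The true AE incidence *t* is the same in both arms. The share of events captured is 0.9 in the Baduanjin arm and *s* in controls. These values are illustrations only.

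**Method**

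The numbers of participants with a recorded event are A ~ Bin(60, 0.9*t*) and B ~ Bin(60, *s·t*). The rejection probability is the sum of P(A = a) × P(B = b) over all tables (a, b) with p < 0.05. It was enumerated exactly for Fisher's exact test and for the chi-squared test without continuity correction. Because true incidence is equal, every rejection is a false positive.

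Example at *t* = 0.30 and *s* = 0.6: expected recorded counts are 60 × 0.30 × 0.9 = 16.2 and 60 × 0.30 × 0.6 = 10.8.

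**False-positive rates**

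| True incidence, both arms | Capture, exercise / control | Chi-squared | Fisher |
|---|---|---|---|
| 15% | 0.9 / 0.9 | 0.047 | 0.026 |
| 30% | 0.9 / 0.9 | 0.053 | 0.030 |
| 5% | 0.9 / 0.6 | 0.060 | 0.011 |
| 10% | 0.9 / 0.6 | 0.092 | 0.040 |
| 15% | 0.9 / 0.6 | 0.119 | 0.069 |
| 30% | 0.9 / 0.6 | 0.222 | 0.157 |
| 5% | 0.9 / 0.4 | 0.094 | 0.018 |
| 15% | 0.9 / 0.4 | 0.284 | 0.179 |
| 30% | 0.9 / 0.4 | 0.553 | 0.459 |

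Equal capture keeps both tests at or below about the nominal level. Unequal capture raises the rate, and more so as events become more common. At 5% incidence the expected recorded counts are only 2.7 and 1.8 (capture 0.9 / 0.6), where Fisher's test is the usual choice, and it stays well below 0.05.

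**Does the test still respond to harm?**

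Yes. With true incidence of 30% against 10% and capture of 0.9 in both arms, power is 0.664 (Fisher) and 0.743 (chi-squared). Capture that is equal but low costs power: at 0.45 in both arms, the figures fall to 0.277 and 0.417. This is what can happen if a narrow definition drops events alike in both arms.

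**The case against.** The strongest reply is that much of this is read from silence. A journal article condenses the full protocol, the schedule figure is not available here, and an AE form or a routine of asking participants may well exist. A reader might infer that reporting is purely passive; the article does not say so, and the lack of a described solicitation procedure is not part of this point.

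The reporting channel as written is also the same in both arms: events go to the research assistants, while the 48 sessions are with coaches. That coach contact raises reporting is a reasonable inference, not a stated rule.

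The word *unexpected* may be loose drafting. The Monitoring section anticipates no harms, so on that view every event is unexpected and nothing is excluded. The Statistical analysis section also refers to AEs without the qualifier. This stands as far as it goes: the article does not establish that foreseeable events will be dropped. But the word sits in the capture rule and permits that, and leaving it to individual judgement is itself a fault.

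Two stronger readings fail. A reader might infer that controls are not seen at all, but they are assessed at week 12 and keep the activity record. A reader might also infer that the test measures ascertainment instead of harm. The power figures show that it responds to real differences, so it mixes the two.

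Finally, the inflation depends on assumed rates and is absent under Fisher's test when events are rare, which is plausible for a low-risk exercise. AEs are neither a primary nor a secondary outcome, and no stopping rule depends on them.

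**Conclusion.** The concern holds in a limited form. The written capture rule can leave out foreseeable exercise complaints. A formal test is also planned on counts from two arms with different described contact, 48 supervised sessions against none between baseline and week 12. Read as a between-group comparison, it confounds harm with opportunity to report.

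The article does not allow the size to be fixed. The inflation set out above arises under moderately unequal capture when events are fairly common, and it disappears under Fisher's test at 5% incidence or less. The possible direction of the bias does not rest on the exact values: better capture in the supervised arm pushes towards an apparent excess with exercise, and equal capture removes that. Importance is minor. It affects how the safety result is read, not the primary analysis.

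**What to change.** 1. Delete *unexpected* from the reporting rule, so that all AEs are recorded.
2. Ask both arms the same short AE question at the same times, through the activity record both already keep and again at week 12.
3. At week 12, have a research assistant put the question, or use a self-completed form, after the outcome measurements. The outcome assessors should not ask it: they are blinded, and an answer about training complaints could reveal allocation.
4. Restrict any between-group AE test to events from this common source. List events noted only at training sessions separately.
5. If common collection is no longer possible, report AEs descriptively by arm and source, without a test, and state that observation differed between arms. The Trial status section says recruitment closed on 30 April 2019 and expects procedures to end by the end of October 2019, so this fallback may apply.

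The cost is one added item in an existing record and one question at week 12. More minor events will need logging, and events before the change remain captured under the old rule. Participants know their allocation, so a common question reduces unequal reporting but cannot remove it entirely.
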